### 5.2.4 Other Subgroup Analysis

Subgroup analyses will be performed for the change in rate pressure product, looking at the homogeneity of the condition effect across the following factors: Sex (Female/ Male) and Site (Montreal/ Sydney).

The subgroup analyses will be conducted using a REML-based linear mixed model, accounting for repeated measures, including a term for condition, a term for the subgroup factor and the condition x subgroup factor interaction. This interaction will be tested at the 0.10 significance level and will determine whether the condition effect is impacted by the presence of the factor. Condition effects will be estimated and presented with 95% confidence interval within subgroups.

The subgroup analysis will be conducted separately under each of the heatwave exposures and will be considered exploratory.

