### *2.2 Research hypotheses:*

The research hypotheses for this study are:

3. In the hot and humid condition, all interventions will result in improved cooling compared to the control (no-fan) trial. With fan and skin-wetting (FSW) being the most effective, then no fan and skin-wetting (NFSW), then fan (F), and finally, the control, no-fan (NF).
4. In the very hot and dry condition, skin wetting with no fan (SWNF) will be the most effective cooling intervention followed by fan and skin-wetting (FSW). We expect the fan (F) intervention to be less effective than the control, no-fan (NF).

*4.3 Participant characteristics:* To complete this study, 56 (greater than or equal to 60 years) adults will be recruited from previous participants who have consented to being contacted for future studies and through the distribution of recruitment flyers at both the Cumberland and Camperdown campuses at The University of Sydney.

*4.4 Sample size:* The sample size computation is based on comparison of the primary endpoint (change in rate pressure product from baseline to the end of a 2 h simulated heatwave exposure to 38°C and 60% relative humidity) between the 4 conditions of control, fan use alone, skin wetting alone, fan use + skin wetting. This preliminary data from young healthy participants was provided by [name], a former PhD student from within our laboratory. A non-repeated measures ANOVA on this data demonstrates 20% (eta squared of 0.2) of the variability was due to the intervention. Using GPower 3.1.9.2 software, an ANCOVA: Fixed effects, main effects and interactions f-test was performed using an alpha of 0.05, beta of 0.1 and an effect size of 0.5 to determine a total sample size of 45 is needed to obtain sufficient statistical power. To account for approximately 20% loss to follow up, 56 participants will be included in the study. Of the 56 participants, 14 will be healthy older females, 14 will be healthy older males, 14 will be healthy females taking antihypertensive medication, and 14 will be older males taking antihypertensive medication.

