### 5.2 Description of the population

Participants will be male or female, aged between 50 and 80 years of age, with stable coronary artery disease.

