## 6- Statistics

### 6.1 Sample size

The sample size computation is based on comparison of the primary endpoint (change in rate pressure product from baseline to the end of a 3 hour simulated heatwave exposure to 38°C and

60% RH) between the 4 conditions of control, fan use alone, skin wetting alone, fan use + skin wetting.

The mean and standard deviation of the change in rate pressure product were taken from the preliminary data presented in Figure 3 and are expected to range between 1000 bpm x mmHg and 1700 bpm x mmHg for the mean and between 1700 bpm x mmHg and 2000 bpm x mmHg for the standard deviation. The standard deviation of the difference between conditions is expected to be similar.

The main interest is to compare the control condition with the 3 other conditions taken individually, which implies a significance level of 0.0167 ( $0.05 / 3$ ). A difference of 1250 bpm x mmHg in change in rate pressure product between the control condition and any other condition is judged to be clinically relevant.

In this context a sample size of 30 participants will give 80% power to detect a difference of 1250 bpm x mmHg in change between the control condition and any other condition, assuming that the standard deviation of the difference between conditions is 2000 bpm x mmHg and using a paired t-test with a 0.0167 two-sided significant level. To account for an approximately 10% loss to follow-up rate, 34 participants will be included in the study. Of the 34 participants, 17 will be taking beta-blockers whereas the other 17 will not be taking beta-blockers.

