## 1 INTRODUCTION

The purpose of this statistical analysis plan (SAP) is to present the statistical methodology that will be used for the final analysis of the combined data from the 2018-496 and 2019-2425 studies performed respectively in Sydney, Australia and Montreal, Canada.

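### The pooled sex subgroup model in SAP 5.2.4 has no site term, so a Montreal–Sydney difference in cooling effect can enter the exploratory condition x sex result

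*Supplement*

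**What the plan says.** SAP Section 1 covers the "final analysis of the combined data from the 2018-496 and 2019-2425 studies". SAP 5.2.4 names two subgroup factors, sex and site. Each is fitted in its own mixed model "including a term for condition, a term for the subgroup factor and the condition x subgroup factor interaction". Of the interaction the SAP says: "This interaction will be tested at the 0.10 significance level and will determine whether the condition effect is impacted by the presence of the factor". It also gives estimates of the cooling effects within each subgroup, with 95% confidence intervals. The subgroup analysis "will be conducted separately under each of the heatwave exposures and will be considered exploratory".

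The two protocols (latest versions) recruit differently:

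- Sydney, Section 4.4: of 56 participants, "14 will be healthy older females, 14 will be healthy older males", and a further 14 women and 14 men take antihypertensive medication. That makes 28 women and 28 men. Section 4.5 excludes beta-blocker users. It also lists, among the exclusions, the absence of a history of CAD. The wording is a double negative, and the evident intent is to keep CAD out.
- Montreal, Section 5.2: "Participants will be male or female, aged between 50 and 80 years of age, with stable coronary artery disease". The only quota is in Section 6.1: "Of the 34 participants, 17 will be taking beta-blockers whereas the other 17 will not be taking beta-blockers". No sex share is set.

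**The concern.** CAD status follows site by design, and sex is balanced at one site only. Unless Montreal enrols equal numbers of men and women, the two sexes in the pooled data contain different proportions of CAD patients. Beta-blocker use, age range and the way the cooling is delivered differ along with CAD. A model with only condition, sex and their interaction cannot separate these differences from sex.

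The documents themselves make a site difference plausible:

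- The Montreal literature review expects the benefit of fan plus wetting to be possibly greatest in CAD patients on beta-blockers.
- Skin is wetted by self-applied sponge at Sydney (Section 4.6) and by spray every 5 minutes at Montreal (Section 5.3.1).
- The fan is at its highest setting at Sydney and is specified as 4.0 m/s at Montreal.
- The SAP considers heterogeneity by site worth testing.

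At stake is the reading of one exploratory interaction and of the within-sex estimates beside it. A sex difference could be suggested, or a real one hidden, by site mix alone.

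**Working it through.** **Inputs from the documents.** Sydney has 28 women and 28 men (Section 4.4). Montreal has 34 participants, an SD of the paired difference of 2000 bpm x mmHg, and a relevant difference of 1250 between control and a cooling condition (Section 6.1). The interaction is tested at 0.10 (SAP 5.2.4).

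**Assumptions, because the documents are silent.** The Montreal male share is taken as 60–90%. The site difference D in one condition effect is taken as 625 or 1250. The true sex interaction is zero. Planned numbers are used with complete data.

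**The plan's own figures.** A paired t-test with n = 30, difference 1250, SD 2000 and two-sided 0.0167 has 80.5% power by the noncentral t, which agrees with the stated 80%. For dropout, 30/0.9 = 33.3, rounded up to 34. The Sydney quotas add up: 4 x 14 = 56.

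**Leakage.** Without a site term, the expected sex contrast is

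false sex difference = [P(Montreal | man) − P(Montreal | woman)] x D.

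| Montreal men/women | P(Montreal, men) | P(Montreal, women) | Gap | D = 625 | D = 1250 |
|---|---|---|---|---|---|
| 17/17 | 17/45 = 0.378 | 17/45 = 0.378 | 0 | 0 | 0 |
| 20/14 (about 60% men) | 20/48 = 0.417 | 14/42 = 0.333 | 0.083 | 52 | 104 |
| 27/7 (about 80%) | 27/55 = 0.491 | 7/35 = 0.200 | 0.291 | 182 | 364 |
| 31/3 (about 90%) | 31/59 = 0.525 | 3/31 = 0.097 | 0.429 | 268 | 536 |

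A female majority at Montreal reverses the sign.

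**Against the noise.** For one contrast with control, SE = 2000 x √(1/men + 1/women), using the pooled totals:

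- 48 men, 42 women: SE 423
- 55 men, 35 women: SE 432
- 59 men, 31 women: SE 444

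At D = 1250 the leakage is therefore 104/423 = 0.25, 364/432 = 0.84 and 536/444 = 1.21 SE. False rejection at the nominal 10% level (noncentral t, 88 df) is 11%, 22% and 33%. At D = 625 it is 10%, 13% and 16%.

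**The full 3-df interaction test.** This was simulated with 4000 runs per setting, four conditions and compound symmetry. At D = 1250 it rejects about 19% of the time with 7 Montreal women and about 30% with 3.

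**With site and condition x site added.** The mean spurious estimate lies between −13 and +13, and rejection is 9–10%, for 3, 5, 7, 10 or 17 Montreal women. A site main effect alone would not do this. A constant shift between sites cancels in each participant's contrast with control, so what leaks is the condition x site difference.

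**The case against.** Four arguments carry weight on the other side.

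First, the analysis is labelled exploratory, no study objective in SAP 2.2 concerns sex, and fitting one factor at a time is a common descriptive choice. This stands, and it limits how much the point matters.

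Second, the same section tests condition x site. With 34 against 56 participants, SE = 2000 x √(1/34 + 1/56) = 435, and that test has about 89% power at 0.10 for a site difference of 1250. A large site difference would therefore usually be flagged next to the sex result. This stands in part: power falls to about 41% at 625, and a warning in one model does not adjust the estimate in another.

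Third, the size rests on quantities that the documents do not give. A reader might infer that 1250 is the expected site difference. It is not: Montreal 6.1 gives it for a cooling condition against control. Used between sites, it would mean, for example, a full relevant benefit at one site and none at the other. That is why 625 is shown as well.

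Fourth, a reader might infer that Montreal's sex mix is whatever CAD clinics supply, and so heavily male. Montreal 5.2.3 lists advertisements, previous participants, people who agreed to contact at annual visits, and prevention clinics. None of these routes fixes the sex ratio, but none establishes a male majority either.

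**Conclusion.** The point holds as a conditional weakness of an exploratory model. Two things must both be true for it to bite: an unequal sex mix at Montreal and a cooling effect that differs by site. Under the stated assumptions the false sex difference is about 50–270 bpm x mmHg (D = 625) or 100–540 (D = 1250), and it is zero at 17/17. Only a strongly unequal mix combined with a large site difference raises the error rate much above nominal. Numbers actually analysed, by sex and site, are not shown and may differ from those planned.

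Two stronger readings are not supported. The documents do not show that the sex result will be wrong, because neither condition is established. Nor is the primary comparison affected by this: it contains no sex term, and its conditions are compared within participants. Sex-specific heat advice is likewise not something the documents plan.

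**What to change.** In SAP 5.2.4, for the 38°C/60% RH exposure, add site and condition x site to the sex subgroup model, so that condition x sex is estimated within site. Condition x site is the term that matters.

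For the 45°C/15% RH exposure, SAP 2.1 schedules the two fan conditions at Sydney only. Make the same addition there for control and skin wetting, and estimate the sex effect for the two fan conditions in Sydney participants alone. Report the numbers of men and women by site beside the results.

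No new data are needed. The price is a slightly wider interval for the sex interaction, more so if Montreal has few women, because the estimate then leans mainly on Sydney. For one contrast, combining within-site estimates by inverse variance, the SE rises from 423 to 424 with 14 Montreal women, from 432 to 452 with 7, and from 444 to 489 with 3. The last follows from Sydney variance 2000² x (1/28 + 1/28) and Montreal variance 2000² x (1/31 + 1/3).

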### 5.2.5 Other exploratory Analysis

To take into account a potential acclimation effect that could occur during the summer, the change in rate pressure product will be analyzed using a REML-based linear mixed model, accounting for repeated measures, including a term for condition, a term for the season (Summer/Not Summer) and the condition x season interaction. This interaction will be tested at the 0.10 significance level and will determine whether the condition effect is impacted by the season. Condition effects will also be estimated and presented with 95% confidence interval within the season category.

The category “Summer” will be assigned to visits that occurred in June, July, August or September at the Montreal site and to visits that occurred in November, December, January, February, March or April at the Sydney site. Otherwise, the “Not Summer” category will be assigned. As season may vary across study visits of a same subject, it will be considered a within-subject factor in the analysis model.

This analysis will be conducted separately under each of the heatwave exposures and will be considered exploratory.

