In Montreal, male or female participants aged between 50 and 80 years of age with stable coronary artery disease were to be included in the study. In Sydney, male or female participants aged 60 years or older were to be included in the study.

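### The exploratory season model in SAP 5.2.5 omits site and condition × site, so part of any site difference in cooling effect is reported as a season effect

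*Supplement*

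**What the plan says.** SAP 5.2.5 analyses the change in rate pressure product with a REML mixed model "including a term for condition, a term for the season (Summer/Not Summer) and the condition x season interaction". For Sydney, Summer covers "visits that occurred in November, December, January, February, March or April at the Sydney site"; for Montreal it runs from June to September. All other visits are Not Summer. On how the result is used: "This interaction will be tested at the 0.10 significance level and will determine whether the condition effect is impacted by the season". Condition effects are also to be reported within each season with 95% intervals. On structure: "As season may vary across study visits of a same subject, it will be considered a within-subject factor in the analysis model". On status: "This analysis will be conducted separately under each of the heatwave exposures and will be considered exploratory".

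Neither site nor coronary artery disease (CAD) status is in this model. Site appears only in the separate subgroup model of SAP 5.2.4, which has no season term.

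**The concern.** The two sites are different populations with different procedures:

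- **Disease.** SAP 2.1: "In Montreal, male or female participants aged between 50 and 80 years of age with stable coronary artery disease were to be included". Sydney took adults aged 60 or older, and its protocol (4.5) lists CAD history under the exclusion criteria.
- **Beta-blockers.** Half of the planned Montreal sample takes them (17 of 34, Montreal protocol 6.1). Sydney excludes users. Rate pressure product contains heart rate, and the SAP itself asks whether beta-blockers alter the cooling effect.
- **Wetting.** Self-applied with a sponge in Sydney (protocol 4.6); sprayed from a bottle every 5 minutes in Montreal (protocol 5.3.1).

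A site difference in cooling effect is therefore plausible, and SAP 5.2.4 plans to look for one. Because the calendar rule gives the sites different Summer shares, the Summer and Not Summer groups have different site mixes. The condition × season term then picks up part of any condition × site difference. A reader told that this test determines whether season matters could take a site difference for acclimation, or miss acclimation that a site difference cancels.

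At 45°C/15% RH there is a further problem. Fan and fan + wetting visits took place only in Sydney (SAP 2.1), whereas control and skin wetting come from both sites. Season-specific fan contrasts there set Sydney-only fan visits against two-site controls.

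**Working it through.** **Inputs.** Planned participants: Sydney 56 (Sydney protocol 4.4), Montreal 34 (Montreal protocol 6.1). SD of the paired difference 2000 and clinically relevant difference 1250 bpm × mmHg (Montreal protocol 6.1). Summer months 6/12 and 4/12, test level 0.10 (SAP 5.2.5). Assumptions not in the documents: the visit calendar, and the site difference in cooling effect D, taken as 625 or 1250 and equal for the three active conditions.

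**The plan's own figure.** The documents give none for the season analysis. The power statement that supplies the SD does reproduce: a paired t-test with n = 30, difference 1250, SD 2000 and two-sided α = 0.0167 has 80.5% power (stated 80%), and 30/0.9 = 33.3, rounded up to 34.

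**Step 1: site mix under even spread.**

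- Summer: Sydney 56 × 0.5 = 28; Montreal 34 × 1/3 = 11.33. Sydney share 28/39.33 = 71.2%.
- Not Summer: Sydney 28; Montreal 22.67. Sydney share 28/50.67 = 55.3%.
- Gap = 0.712 − 0.553 = 0.159.

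**Step 2: leak.** If each participant's visits fall in one season, the expected false season difference is gap × D: 0.159 × 625 ≈ 100 and 0.159 × 1250 ≈ 199. If season varies from visit to visit, simulation gives somewhat more: about 130 for D = 625 and about 250 for D = 1250. The leak is thus about 16–20% of D.

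**Step 3: effect on the 0.10 test (3 df).** A paired-difference SD of 2000 gives a residual variance of 2000²/2 = 2,000,000 under compound symmetry. For an equal shift b in the three contrasts, the noncentrality is 0.75 × b² / [2,000,000 × (1/n₁ + 1/n₂)]. With b = 199, n₁ = 39.33 and n₂ = 50.67 this is 0.33, and the test rejects about 13% of the time.

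Simulation with no true season effect (90 participants × 4 conditions, 1,000 to 3,000 runs per scenario):

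| Summer share, Sydney / Montreal | Gap | Leak, D = 1250 (gap × D) | Rejection, D = 625 | Rejection, D = 1250 |
|---|---|---|---|---|
| 50% / 50% (assumed) | 0 | 0 | about 10% | about 10% |
| 50% / 33% (even spread) | 0.159 | 199 | 11% | 13–18% |
| 60% / 20% (assumed) | 0.380 | 475 | 15% | 27–33% |
| 70% / 10% (assumed) | 0.566 | 707 | not tabulated | 50–56% |

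The ranges cover season fixed within participant and season varying by visit. With D = 0 rejection stays near 10%.

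**Step 4: with site and condition × site added.** In the simulated scenarios, rejection returns to 9–12% and the mean false interaction lies within about ±31 of zero.

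**Step 5: does treating season as within-subject remove the problem?** No. A participant-level term absorbs a site difference that is the same in all conditions. It does not absorb one that differs by condition, and the leak persists when season varies by visit.

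**The case against.** - **The analysis is exploratory.** This stands. The primary (SAP 5.2.1) and secondary (SAP 5.2.2) models contain no season term. A reader might infer that the main cooling comparisons are biased by this; the documents do not support that.
- **SAP 5.2.4 already tests condition × site.** This stands in part. With D = 1250 the noncentrality of that test is 0.75 × 1250² / [2,000,000 × (1/34 + 1/56)] = 12.4, which gives about 91% power at 0.10. A site difference that large would usually be visible elsewhere in the report. At D = 625 power is only about 40%, and in neither case is the season estimate corrected.
- **The large distortions rest on invented calendars.** This stands. No section gives visit dates. The 60/20 and 70/10 rows show sensitivity only, and D itself is assumed.
- **The Summer definitions might look like the error.** They are not. Site-specific months are needed for opposite hemispheres; the fault is leaving site out.
- **The 72-hour gap might suggest that most participants finish within one season.** It is a minimum, with no maximum or typical spacing given, and SAP 5.2.5 allows season to vary within a participant. The point does not depend on this.
- **Condition × site cannot be fitted in full at 45°C/15% RH.** This stands. Montreal has no fan cells there, so the remedy must differ by exposure.

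**Conclusion.** The point holds as a modest, fixable flaw in an exploratory analysis. As written, the model cannot separate a season effect from a site difference in cooling effect. Under even spread and planned numbers, about 16–20% of that site difference is reported as season, and the 0.10 test rejects about 11–18% of the time for D between 625 and 1250. It would be worse only if the sites' Summer shares differ more than the calendar rule alone implies. There is no bias if the Summer shares are equal or the sites do not differ in cooling effect. The sizes rest on the assumed visit calendar, the assumed D, the planned rather than achieved numbers, and the Montreal SD applied to both sites. They were worked out for the four-condition 38°C/60% RH layout; no figure is given for 45°C/15% RH.

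**What to change.** In SAP 5.2.5:

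1. At 38°C/60% RH, add site and condition × site (3 df for the interaction), so that condition × season is estimated within site.
2. At 45°C/15% RH, fit the site-adjusted season model to control and skin wetting only (1 df for condition × site). Estimate the season contrasts for fan and fan + wetting in a Sydney-only model.
3. Tabulate visits by site, season and condition, so that the actual overlap can be seen.

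Site is already used in SAP 5.2.4, so no new data are needed. The cost is the extra model terms, one additional Sydney-only model, one table, and a somewhat wider interval on the season interaction.
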